### Experimental procedures

#### Transcranial magnetic stimulation (TMS)

A figure-of-8 coil connected to two Magstim 200^2^ magnetic stimulators (Magstim, Dyfed, UK) via a BiStim unit will be used to apply TMS to the left M1. The coil will be held tangentially to the scalp, at an angle of 45° to the sagittal plane, with the handle pointing backwards and laterally, inducing a posterior-to-anterior (PA) current within the brain. The location producing the largest and most consistent motor evoked potential (MEP) within the relaxed FDI muscle of the right hand will be identified and marked on the scalp for reference; this target location will be closely monitored throughout the experiment. All pre- and post-intervention TMS will be applied at a rate of 0.2 Hz, with a 10% jitter between trials in order to avoid anticipation of the stimulus.

Resting motor threshold (RMT) will be defined as the stimulus intensity producing an MEP amplitude ≥ 50 μV in at least 5 out of 10 trials during relaxation of the right FDI. RMT will be assessed at the beginning of each experimental session and expressed as a percentage of maximum stimulator output (%MSO). Following assessment of RMT, the stimulus intensity producing a standard MEP amplitude of approximately 1 mV (MEP_*1mV*_), when averaged over 20 trials, will be identified. The same intensity will then be applied 5 mins and 30 mins following the intervention in order to assess changes in corticospinal excitability.

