#### I-wave excitability

As assessing the influence of CB modulation on I-wave excitability is the main aim of this project, changes in SICF will be the primary outcome measure. This paired-pulse TMS protocol produces MEP facilitation when conditioning and test stimuli are separated by discrete ISIs that correspond to I-wave latencies recorded from the epidural space [22]. SICF will utilise a conditioning stimulus set at 90% RMT, a test stimulus set at MEP_*1mV*_ and two ISIs of 1.5 and 4.5 ms, which correspond to the early and late MEP peaks apparent in a complete SICF curve [22, 25, 26]. Measurements of SICF will include 12 trials for each condition, at each time point.

As a secondary measure of I-wave function, TMS will be applied with different stimulus directions, which alters the interneuronal circuits contributing to the generated MEP [16, 27, 28]. When TMS is applied with a conventional (PA) current direction, the resulting MEP is thought to arise from preferential activation of early I1-waves. In contrast, when the induced current is directed from anterior-to-posterior (AP; coil handle held 180° to the PA orientation), the resulting MEP is thought to arise from preferential activation of later (I2-3) I-waves. The stimulus intensity producing an MEP of approximately 0.5 mV will be assessed for both PA (MEP_*PA*_) and AP (MEP_*AP*_) orientations at baseline. The same intensities will then be reapplied 5 mins and 30 mins after the intervention, with 20 trials applied at each time point. While the I-wave specificity of these measures is generally suggested to rely on concurrent activation of the target muscle [27], post-intervention muscle activation is also known to strongly influence neuroplasticity induction [29–31]. As the current study is primarily concerned with plasticity induction, these measures will therefore be applied in a resting muscle in order to minimize confounding effects of voluntary contraction. Given the likely independence of the intracortical circuits activated with different currents, these measures will still provide useful physiological insight.

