### Data analysis

Analysis of EMG data will be completed manually via visual inspection of offline recordings. For measures in resting muscle, any trials with EMG activity exceeding 25 μV in the 100 ms prior to stimulus application will be excluded from analysis. All MEPs will be measured peak-to-peak and expressed in mV. Measures of CBI will be quantified by expressing the amplitude of individual trials produced by paired-pulse stimulation as a percentage of the mean response produced by single-pulse stimulation within the same block. For baseline measures of SICF, individual trials produced by paired-pulse stimulation will be expressed as a percentage of the mean response produced by single-pulse stimulation within the same block. However, for post-intervention responses, previous work has suggested that increased facilitation following iTMS correlates with the increased response to single pulse stimulation, and that this relationship cancels the effects of iTMS on SICF if the post-intervention single-pulse MEPs are used to normalise post-intervention SICF values [21]. Consequently, prior to normalization of post-intervention SICF values, we will use linear regression analysis to assess the relationship between post-intervention single and paired-pulse responses. If the relationship is significant, individual post-intervention SICF trials will be expressed relative to the mean pre-intervention single-pulse MEP [21]. However, if the relationship is not significant, post-intervention SICF measures will be expressed relative to the single-pulse response recorded in the same block. For all TMS measures, effects of the intervention will be quantified by expressing the post-intervention responses (normalised to the relevant single-pulse response for CBI and SICF) as a percentage of the pre-intervention responses.

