### Statistical analysis

Kolmogorov-Smirnov tests will be applied to assess data distribution prior to statistical analysis, with log transformation applied when deviations from normal are indicated. Given that all data of interest will involve repeated-measures, linear mixed-model analysis with repeated-measures (LMM_*RM*_) will be used to perform all statistical comparisons. Each model will include single trial data, and previously reported methods [38] will be used to justify inclusion of random participant intercepts and/or slopes, and to optimize and assess model fit. To ensure measures are comparable between sessions, effects of iTMS session (iTMS_*1*.*5*_, iTMS_*4*.*5*_ & iTMS_*Sham*_) on baseline measures of MEP_*1mv*_, MEP_*PA*_, MEP_*AP*_ and CBI, in addition to responses recorded at the start of the iTMS intervention, will be investigated using one-factor LMM_*RM*_, with each measurement investigated in a separate model. Furthermore, effects of iTMS session and ISI (1.5 & 4.5 ms) on baseline SICF will be assessed using two-factor LMM_*RM*_.

Changes in excitability during the intervention will be assessed by comparing values averaged over the first, middle and last 12 stimuli of the iTMS block between iTMS sessions. Changes in corticospinal excitability following the intervention will be investigated by assessing the effects of iTMS session and time (Post 5, Post 30) on baseline-normalised MEP_*1mV*_ values. Changes in coil-orientation dependent measures of I-wave excitability following the intervention will be investigated by assessing effects of iTMS session, time and coil orientation (MEP_*PA*_, MEP_*AP*_) on baseline-normalised values. Changes in SICF measures of I-wave excitability following the intervention will be investigated by assessing effects of iTMS session, time and ISI on baseline-normalised values. Changes in CBI following the intervention will be investigated by assessing the effects of iTMS session and time on baseline-normalised CBI values. For all models, investigation of main effects and interactions will be performed using custom contrasts with Bonferroni correction, and significance will be set at *P* < 0.05. Data for all models will be presented as the estimated marginal means, whereas pairwise comparisons will be presented as the estimated mean difference (EMD) and 95% confidence interval (95%CI) for the estimate, providing a non-standardised measure of effect size.

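### Post/pre percentages with logs triggered by a Kolmogorov-Smirnov test: fix the log scale in advance and adjust for log baseline instead of dividing by it

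*Protocol article*

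**What the plan says.** Data analysis: "For all TMS measures, effects of the intervention will be quantified by expressing the post-intervention responses" (SICF and CBI having first been divided by a single-pulse mean) "as a percentage of the pre-intervention responses". For SICF, the primary outcome, if a preliminary regression is significant, "individual post-intervention SICF trials will be expressed relative to the mean pre-intervention single-pulse MEP".

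Statistical analysis: "Each model will include single trial data". The post-intervention models use baseline-normalised values, and their time factor has two levels, 5 and 30 minutes after the intervention. Baseline therefore enters these models only as a divisor. The scale is chosen as follows: "Kolmogorov-Smirnov tests will be applied to assess data distribution prior to statistical analysis, with log transformation applied when deviations from normal are indicated". The during-intervention analysis works on another level of data, "comparing values averaged over the first, middle and last 12 stimuli of the iTMS block between iTMS sessions". Results are reported as estimated marginal means, with mean differences for pairwise comparisons.

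Baselines are short and some are titrated. I-wave excitability: "Measurements of SICF will include 12 trials for each condition, at each time point". CBI has 15 trials per condition and time point; the PA, AP and 1 mV measures have 20. Under Transcranial magnetic stimulation (TMS), each session sets "the stimulus intensity producing a standard MEP amplitude of approximately 1 mV". The PA and AP measures are set to about 0.5 mV in the same way.

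The article does not say at which level the K-S test is run, or whether logs are taken before or after normalisation.

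**The concern.** Three features of this scale deserve attention.

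1. Dividing by baseline is the same as fixing the slope of log post on log baseline at 1. Where the stimulus is titrated to a target amplitude, a participant's baselines may differ between sessions mainly through sampling error. Division then adds that error to the outcome. All post trials of a session share the same divisor, so recording more post trials does not average the error out.
2. A normality test used as a switch responds to the number of values as well as to their shape. Skewed amplitudes may be logged in one analysis and left raw in another.
3. The mean of logs is not the log of the mean. If a trial is divided by an arithmetic baseline mean and then logged, its expected value under no change lies below log(100%).

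At stake are the precision of the contrasts, a common scale across models, and whether a reported marginal mean below 100% indicates inhibition.

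**Working it through.** The plan gives no figure on this point. From the documents I take 21 participants, 3 sessions, 2 post times, 2 SICF ISIs, and 12, 15 or 20 baseline trials. Trial-to-trial CV is assumed to be 0.3 to 1.0 with lognormal amplitudes, because the article gives no value.

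**1. Baseline noise and slope**

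- The SD of the log of an m-trial baseline mean is about CV/√m. For CV 0.5 and m = 12 this is 0.5/3.46 = 0.14 (simulated 0.143). The simulated values for CV 0.3, 0.7 and 1.0 are 0.09, 0.20 and 0.28.
- Let k be the SD of the within-participant session difference at baseline divided by that at post, and rho the correlation of the two differences. The variance of the covariate-adjusted contrast over that of the change score is (1 − rho²)/(1 + k² − 2·rho·k). It never exceeds 1, and equals 1 when the true slope rho/k is 1.
- k = 1: 0.65 at rho 0.3 and 0.75 at rho 0.5.
- k = 0.7: 0.91/1.07 = 0.85 and 0.75/0.79 = 0.95.
- k = 0.5: 0.91/0.95 = 0.96 and 0.75/0.75 = 1.00.
- Simulation (21 participants, 2 sessions, 12 trials, log response SD 0.2 assumed):

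| SD of true session-level baseline (log) | Change/adjusted variance, CV 0.5 | Change/adjusted variance, CV 0.7 |
|---|---|---|
| 0.0 | 1.30 | 1.39 |
| 0.1 | 1.16 | 1.32 |
| 0.2 | 1.03 | 1.16 |
| 0.3 | 1.00 | 1.04 |

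The saving is 1 − 1/ratio, so it runs from 0% (ratio 1.00) to 1 − 1/1.39 = 28%. The k = 1 cases above correspond to 25% and 35%.

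**2. K-S verdict and number of values**

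- Independent lognormal values with CV 0.5, plain K-S with estimated mean and SD: rejection in 1.4% at n = 21, 94% at n = 21 × 12 = 252, and 100% at n = 21 × 3 × 2 × 2 × 12 = 3,024 (all post-intervention SICF trials).
- Simulated baseline-normalised data with participants, sessions and times: at trial level (21 × 3 × 2 × 12 = 1,512 values) rejection is 100% at every CV tried. On 21 participant means it is 0-1% with plain K-S and 8-24% with the Lilliefors correction.

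**3. No-change value after logging**

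With s² = ln(1 + CV²), a trial divided by an m-trial arithmetic mean has expected log of about −s²/2 + CV²/(2m) under no change.

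| CV | s² | exp(−s²/2) | with m = 12 | simulated, m = 12 |
|---|---|---|---|---|
| 0.3 | 0.086 | 95.8% | 96.1% | 96.1% |
| 0.4 | 0.148 | 92.8% | 93.5% | not run |
| 0.5 | 0.223 | 89.4% | 90.4% | 90.4% |
| 0.7 | 0.399 | 81.9% | 83.6% | 83.6% |
| 1.0 | 0.693 | 70.7% | 73.7% | 73.6% |

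For SICF the same value applies under either normalisation rule. With the pre-intervention single-pulse mean, that mean cancels exactly. With the same-block mean, the pre and post single-pulse terms cancel in expectation under no change, given equal trial numbers.

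Without logs, the no-change mean is slightly above 100%: about 1 + CV²/m, or 102.1% at CV 0.5 and m = 12.

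A contrast between two conditions with CVs c1 and c2 shifts by the factor √[(1 + c2²)/(1 + c1²)]. This is 1.00 if they are equal, √(1.16/1.25) = 0.96 for 0.5 against 0.4, and √(1.25/1.49) = 0.92 for 0.7 against 0.5.

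**The case against.** The main objections, and what stands of each:

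- **Titration error is not all noise.** The same intensity is reapplied after the intervention, so a session that truly starts at 1.2 mV carries that level forward and a slope near 1 is right for that part. This stands, and it is why the saving can be nil. SICF, the primary outcome, is moreover a paired-to-single ratio and is not itself titrated. An estimated slope covers both situations.
- **A reader might infer a specific power gain.** With the article's effect size of 0.67, n = 21 and k = 1, two-sided power would rise from 83% to 95% (rho 0.3) or 92% (rho 0.5). The documents do not support this. Equal baseline and post variance sits badly with titrated baselines, and at k = 0.5 to 0.7 power is only 83-89%. The 0.67 is also a SICF effect from another study, while the titration argument concerns other measures. No power figure should be claimed.
- **The scale is hardly unstable.** Single-trial models suggest a trial-level test, where logging is almost certain. This largely stands for the post-intervention models. The risk of mixed scales is mainly between these and the averaged during-iTMS comparison.
- **The shift needs steps the article does not spell out.** It requires logging after division, and a back-transformed mean read against 100%. The order is the natural reading of single-trial, baseline-normalised data, but it is not stated. No test against 100% is planned, so a reader who inferred that the planned session tests are biased towards inhibition would go too far.

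**Conclusion.** The point holds as a cheap improvement to an exploratory study's analysis, not as a flaw that invalidates the planned tests.

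- **Precision.** Baseline adjustment on the log scale is asymptotically never worse than division. The gain ranges from near zero, when true session-level baseline differences or response variability dominate, to roughly 20-30% or more of contrast variance when baselines differ mainly by sampling noise. It is not shown that precision is lost on every outcome.
- **Scale.** The K-S rule would almost always log trial-level MEPs but might leave averages raw.
- **Reference value.** If logs follow division, no change sits at about 93%, 90% and 84% for CV 0.4, 0.5 and 0.7 with 12 baseline trials. This distorts marginal means read as increase or decrease. It cancels in session contrasts when trial variability is equal, but not in orientation or ISI contrasts when it differs.

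Every size rests on assumed CVs, correlations and lognormal amplitudes. The direction of the shift does not depend on the CV.

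**What to change.** - Set the log scale in advance for all MEP outcomes, remove the K-S trigger, and check model residuals instead.
- Model log post-intervention values without dividing by baseline. Use as covariates the session's log baseline (mean of the logged trials, centred within participant) and the participant's mean log baseline.
- Report geometric-mean ratios: the exponential of the adjusted mean log post value, evaluated at the overall mean log baseline, minus that baseline mean. No change is then 100% by construction.
- Where SICF or CBI is related to a single-pulse response, take that reference as a mean of logs too. Which single-pulse block serves as the SICF reference is a separate question that this change does not settle.

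The cost is a change of analysis wording and one or two degrees of freedom, with no new data or visits. Results become geometric-mean ratios, which are not directly comparable with arithmetic percentages.

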### Statistical analysis

Kolmogorov-Smirnov tests will be applied to assess data distribution prior to statistical analysis, with log transformation applied when deviations from normal are indicated. Given that all data of interest will involve repeated-measures, linear mixed-model analysis with repeated-measures (LMM_*RM*_) will be used to perform all statistical comparisons. Each model will include single trial data, and previously reported methods [38] will be used to justify inclusion of random participant intercepts and/or slopes, and to optimize and assess model fit. To ensure measures are comparable between sessions, effects of iTMS session (iTMS_*1*.*5*_, iTMS_*4*.*5*_ & iTMS_*Sham*_) on baseline measures of MEP_*1mv*_, MEP_*PA*_, MEP_*AP*_ and CBI, in addition to responses recorded at the start of the iTMS intervention, will be investigated using one-factor LMM_*RM*_, with each measurement investigated in a separate model. Furthermore, effects of iTMS session and ISI (1.5 & 4.5 ms) on baseline SICF will be assessed using two-factor LMM_*RM*_.

Changes in excitability during the intervention will be assessed by comparing values averaged over the first, middle and last 12 stimuli of the iTMS block between iTMS sessions. Changes in corticospinal excitability following the intervention will be investigated by assessing the effects of iTMS session and time (Post 5, Post 30) on baseline-normalised MEP_*1mV*_ values. Changes in coil-orientation dependent measures of I-wave excitability following the intervention will be investigated by assessing effects of iTMS session, time and coil orientation (MEP_*PA*_, MEP_*AP*_) on baseline-normalised values. Changes in SICF measures of I-wave excitability following the intervention will be investigated by assessing effects of iTMS session, time and ISI on baseline-normalised values. Changes in CBI following the intervention will be investigated by assessing the effects of iTMS session and time on baseline-normalised CBI values. For all models, investigation of main effects and interactions will be performed using custom contrasts with Bonferroni correction, and significance will be set at *P* < 0.05. Data for all models will be presented as the estimated marginal means, whereas pairwise comparisons will be presented as the estimated mean difference (EMD) and 95% confidence interval (95%CI) for the estimate, providing a non-standardised measure of effect size.

Regression analyses will be used to investigate interactions between variables. Specifically, changes in CBI due to the intervention will be regressed against changes in measures of corticospinal and intracortical function in order to assess if alterations within the CB-M1 pathway contribute to plasticity effects. In addition, changes in intracortical function due to the intervention will be regressed against changes in corticospinal function in an attempt to identify if generalised changes in excitability are driven by alterations within specific circuits.

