#### I-wave periodicity repetitive TMS (iTMS)

In accordance with previous literature [21, 35], iTMS will consist of 180 pairs of stimuli applied every 5 s, resulting in a total intervention time of 15 mins. The same intensity will be used for both stimuli, adjusted to produce a response of ~ 1mV when applied as a pair. These stimuli will be applied using ISI’s of 1.5 (iTMS_*Early*_) and 4.5 ms (iTMS_*Late*_) in separate sessions. These parameters produce robust potentiation of MEP amplitude [20, 21, 35, 36]. A sham stimulation condition (iTMS_*Sham*_) that is not expected to modulate corticospinal excitability will also be applied in a third session. Within this condition, we will stimulate intervals that correspond to the transition between the peaks and troughs of facilitation that are observed within a complete SICF curve, as these are not expected to induce any changes in excitability. This will include equal repetitions of 1.8, 2.3, 3.3, 3.8 and 4.7 ms ISI’s, applied randomly and with an inter-trial jitter of 10%.

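### The 12-stimulus windows do not balance the five sham ISIs, so sham means during iTMS carry avoidable random variation that the single-ISI active sessions lack

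*Protocol article*

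**What the plan says.** All places are in the Methods of the Protocol article.

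- **I-wave periodicity repetitive TMS (iTMS), block:** "iTMS will consist of 180 pairs of stimuli applied every 5 s, resulting in a total intervention time of 15 mins".
- **Same section, active sessions:** "These stimuli will be applied using ISI’s of 1.5 (iTMS_*Early*_) and 4.5 ms (iTMS_*Late*_) in separate sessions". Every pair in an active session therefore has the same ISI.
- **Same section, sham session:** "equal repetitions of 1.8, 2.3, 3.3, 3.8 and 4.7 ms ISI’s, applied randomly and with an inter-trial jitter of 10"% between trials. The equality applies to the block; nothing is said about any part of it. The sham ISIs are chosen as "intervals that correspond to the transition between the peaks and troughs of facilitation that are observed within a complete SICF curve".
- **Same section, intensity:** "The same intensity will be used for both stimuli, adjusted to produce a response of ~ 1mV when applied as a pair". Which sham ISI is used for that adjustment is not stated.
- **Statistical analysis, during the intervention:** the analysis proceeds by "comparing values averaged over the first, middle and last 12 stimuli of the iTMS block between iTMS sessions". The section also says that the models use single-trial data. It names ISI as a factor for SICF, but not for the iTMS block.
- **Statistical analysis, comparability check:** baseline measures, "in addition to responses recorded at the start of the iTMS intervention, will be investigated using one-factor LMM_*RM", with session as the factor. How many stimuli count as the start is not stated.

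**The concern.** The section on I-wave excitability bases SICF on the fact that paired-pulse facilitation depends on ISI. The sham ISIs lie on the slopes between peaks and troughs, and the article does not say that all five give the same response. If they do not, the mean of a sham window depends partly on which ISIs fell into it. That mix changes by chance from the first window to the middle to the last. An active session has no such component, because its ISI is constant.

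At stake is the precision of the sham comparator in the one stated analysis of excitability change during the intervention. The check of responses at the start of iTMS may also be affected, depending on which stimuli it uses.

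**Working it through.** **Inputs from the article.** 180 pairs, one every 5 s; five sham ISIs in equal repetitions and random order; windows of 12 stimuli.

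**Assumptions.** Simple random order of the 180 pairs, since no restriction is stated. The spread *s* of the five ISI means (log-SD 0.1, 0.2, 0.3) and the trial log-SD (0.5) are not in the article.

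**Step 1. The article's own figures.** 180 × 5 s = 900 s = 15 min, as stated. 180/5 = 36 repetitions per sham ISI.

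**Step 2. Composition of one sham window.**
- Expected count per ISI: 12/5 = 2.4, the same in the first, middle and last window.
- SD of a count (hypergeometric): √(12 × 0.2 × 0.8 × 168/179) = 1.34.
- Probability that at least one ISI is absent, by inclusion–exclusion: [5·C(144,12) − 10·C(108,12) + 10·C(72,12) − 5·C(36,12)] / C(180,12) = 0.3120 − 0.0168 + 0.0001 − 0.0000 = 0.295.
- Probability of the most even split (3,3,2,2,2): 10·C(36,3)²·C(36,2)³ / C(180,12) = 0.077.
- By simulation (100,000 sessions), first and last windows have the same mix in about 0.2% of sessions. On average 3.8 of the 12 stimuli differ in ISI.

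**Step 3. Bias.** Expected counts are equal in all windows, so the expected composition effect on any change between windows is 0.

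**Step 4. Added variance of a sham window mean.** Composition variance is (s²/12)(168/179) and trial variance is 0.5²/12. The ratio is 0.9385·s²/0.25. For the active-versus-sham contrast in a window, with equal trial noise in both sessions, the SE multiplier is √(1 + ratio/2).

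| Assumed ISI log-SD | Variance ratio | Rise in sham window-mean variance | SE multiplier of contrast | Rise in SE of contrast |
|---|---|---|---|---|
| 0.1 | 0.038 | about 4% | 1.009 | about 1% |
| 0.2 | 0.150 | about 15% | 1.037 | about 4% |
| 0.3 | 0.338 | about 34% | 1.081 | about 8% |

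If the five ISIs give equal responses (s = 0), nothing is added.

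**Step 5. What drives it.** The SD of the composition part of the last-minus-first sham change in one session, at s = 0.3:
- 12-stimulus windows, simple random order: 0.3 × √((180/179)(2/12)) = 0.123.
- 15-stimulus windows, simple random order: 0.3 × √((180/179)(2/15)) = 0.110.
- 12-stimulus windows, order permuted in blocks of five: each window is two full blocks plus two stimuli of a third, so the SD is 0.3 × √(3/144) = 0.043.
- 15-stimulus windows aligned to blocks of five: 0.

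A window length divisible by five gains little on its own. The unrestricted order is the main source.

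**The case against.** **A reader might infer that the sham comparison is confounded with ISI composition.** The article does not support that. Under random order each window has the same expected mix, so the group-level expectation is unaffected. A systematic shift would need one order reused for every participant, which the article does not say. A chance trend in one participant's sham session is possible, but the stated comparisons are at group level.

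**A reader might blame the choice of 12, because it is not a multiple of five.** Step 5 shows this is a minor part: 15 stimuli in simple random order leave nearly the same noise.

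**A reader might assume that the first 12 stimuli also serve the start-of-iTMS check.** The article does not define which stimuli that check uses.

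**The size is unknown.** This stands. The sham ISIs were chosen away from the extremes of facilitation, which may make their responses more alike than peaks and troughs would be. The spread could be small, and the effect then negligible.

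**The sequence scheme may be fixed in a full protocol or stimulus script.** This stands in part. The figures in step 2 apply only to unrestricted order, and if the order is already blocked most of the problem disappears.

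**Single-trial models could carry an ISI term.** They could, and this is a good remedy. But the section names ISI where it is meant as a factor, for SICF, and describes this comparison in terms of averaged values.

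**Conclusion.** The point holds as a minor matter of precision. As written, the plan sets a randomly ordered five-ISI sham against single-ISI active sessions in short windows, with no stated balancing or adjustment. Under simple random order, sham means during the intervention carry noise that the active means do not.

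Over the assumed spreads, the cost is about 1% to 8% on the SE of the active-versus-sham contrast, and zero if the sham ISIs give equal responses. Variation between participants and sessions would dilute it further. The conclusion rests on simple random order, on orders independent between participants, and on the assumed SDs.

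It bears on the during-intervention comparison and possibly the start-of-iTMS check. It does not bear on the primary SICF outcome or the other post-intervention measures, which do not use these windows.

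**What to change.** 1. Generate the sham ISI order in permuted blocks of five (36 blocks), with a new order for each participant.
2. Use windows of 15 stimuli in all three sessions, aligned to those blocks: for example stimuli 1–15, 81–95 and 166–180. Each sham window as delivered then holds exactly three of each ISI. Alignment matters: a middle window centred on the block's midpoint (between stimuli 90 and 91) would cut across blocks and lose the exact balance.
3. Include ISI as a term for the sham trials in the single-trial model. This handles the imbalance left when trials are excluded for pre-stimulus EMG activity, and it would help even if the order and windows stayed as they are.
4. State which stimuli make up the start-of-iTMS check, and use the first block-aligned window for it.

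**Cost:** a restricted randomisation list, a middle window slightly off centre (centred on stimulus 88 rather than 90.5, which is 2.5 × 5 s = 12.5 s early), slightly longer windows and a few more model parameters. The number of pairs, the ISIs, the intensity and the timing do not change.
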